### Interventions

This trial will include two groups: the TEAS group and the group receiving transcutaneous acupoint pseudoelectric stimulation (Sham TEAS). In each group, there will be 44 patients receiving CABG with CPB. The patients of the TEAS group will receive TEAS therapy in the perioperative period, and in the Sham TEAS group, pseudotherapy without actual electrical stimulation will be performed in the perioperative period. The intervention details are as follows:
Selection of acupoints: Zusanli acupoint (ST36), Shenshu acupoint (BL23) (see Figs. 2 and 3):
Zusanli location: outside of the shank, 3 cun (10 cm) below Dubi acupoint (ST35) and a finger’s width (middle finger) to tibial front edgeShenshu location: below the spinous process of the second lumbar vertebra, 1.5 cun (5 cm) to the central lineStimulation timing: before anesthesia plus intraoperative plus postoperative (see Fig. 4):
30 min before anesthesia: one stimulation for 30 minIntraoperative: stimulation for the whole coursePostoperative: 0–24 h: four times of stimulation (30 min per stimulation). 5–6 h after the surgery (the first time), 11–12 h after the surgery (the second time), 17–18 h after the surgery (the third time), 23–24 h after the surgery (the fourth time)TEAS parameters
Frequency: 2/100 Hz alternatingIntensity: 15 mALow-frequency electronic pulse therapeutic device G6805-2 (Huayi, Shanghai, China) (see Fig. 5)Current intensity: main difference between the study group and control group
TEAS group: the acupoints, including Zusanli and Shenshu, are identified before electrical stimulation with surface electrodes (Fig. 6). Selection of these acupoints was based on a consensus between the acupuncturists of the study.Sham TEAS group: No electrical stimulation is actually performed in the Sham TEAS group. In the Sham TEAS group, pseudostimulation is provided by deliberately connecting the electrodes to the incorrect output socket of the EA device; thus, there is no flow of electric current. Patients can see the output light flashing, but no current is transmitted throughout the procedure. Patients would be told that the stimulation frequency selected was not perceivable by humans.Anesthesia protocol
Medication before the anesthesia: morphine 0.1 mg/kgAnesthesia induction
Sufentanil 0.3–0.5 μg/kgPropofol, target-controlled infusion (TCI): 2.0–3.5 μg/mlDextromidine 0.5–1.0 μg/kg/h or midazolam 0.05–0.1 mg/kgLidocaine 1 mg/kg (maximum dose not higher than 50 mg)Rocuronium bromide 0.9–1.2 mg/kgMaintenance of anesthesia
Narcotic analgesics: common sufentanil by 0.2–0.5 μg/kg by times (intravenously) or remifentanil by 0.05–0.2 μg/kg/min continuous intravenous pump injection, addition of sufentanil by 10–20 μg before skin incision and sternum splitting.Inhaled general anesthetics: sevoflurane and isoflurane can be inhaled discontinuously as requested with minimum alveolar concentration (MAC) 0.7–1.0.Muscle relaxant: common vecuronium bromide and rocuronium bromide, etc.After the completion of tracheal intubation, the anesthesia machine is connected immediately, and end-tidal carbon dioxide (ETCO_2_) is examined, and the breathing sound of both lungs is auscultated to determine the position of endotracheal tube.Common parameters of mechanical ventilation: tidal volume (VT) 7–8 ml/kg, respiratory rate (RR) 10–12 bpm, arterial partial pressure of oxygen (PaO_2_) 200 mmHg, arterial partial pressure of carbon dioxide (PaCO_2_) 35–45 mmHg, fraction of inspired oxygen (FiO_2_) 80%.

**Fig. 2 Fig2:**
[figure not shown]
Zusanli location: outside of the shank, 3 cun(10 cm) below Dubi acupoint and a finger’s width (middle finger) to tibial front edge

**Fig. 3 Fig3:**
[figure not shown]
Shenshu location: below the spinous process of the second lumbar vertebra, 1.5 cun (5 cm) to the central line

**Fig. 4 Fig4:**
[figure not shown]
The patients will receive TEAS therapy 30 min before anesthesia (one stimulation for 30 min), during the period of surgery (stimulation for the whole course) and within 24h after surgery (four times of stimulation, each for 30min)

**Fig. 5 Fig5:**
[figure not shown]
We will use Low-frequency electronic pulse therapeutic device G6805-2 (Huayi, Shanghai, China) for TEAS therapy, the frequency will be 2/100 Hz alternating and the intensity will be 15mA

**Fig. 6 Fig6:**
[figure not shown]
**a**: Patient received TEAS therapy at bilateral Zusanli acupoint (ST36) and Shenshu acupoint (BL23) during the perioperative period. **b**: Zusanli acupoint (ST36) is identified. **c**: Shenshu acupoint (BL23) is identified

### Outcomes

#### Primary outcome measures

With mHLA-DR as the primary outcome of this clinical trial, the improvement of postoperative immunosuppression will be evaluated.

Peripheral blood is collected from the patient to test this indicator at the following time points: one day before surgery, Day 1 after surgery (one day after surgery), Day 3 after surgery (3 days after surgery), and Day 5 after surgery (5 days after surgery).

The percentage of HLA-DR^+^/CD14^+^ cells in all CD14^+^ cells will be determined by flow cytometry (Becton-Dickinson, Franklin Lakes, NJ, USA) in the central lab of Shuguang Hospital Affiliated to Shanghai University of Traditional Chinese Medicine.

#### Secondary outcome measures

The secondary outcome measures are as follows:
Related indicators of immunosuppression include interleukin (IL)-6, IL-10, C-reactive protein (CRP), postoperative infectious complications (pneumonia, incision infection, and indwelling catheter infection), ICU stay time, and mortality. The examination methods and time points are as follows:
IL-6 and IL-10: Plasma levels of IL-6 and IL-10 will be determined using the ELISA (enzyme-linked immunosorbent assay) with high sensitivity kits (ABCAM, Shanghai, China) one day before surgery and on Days 1, 3, and 5 after surgery.CRP: CRP expression level in blood samples, determined with automatic biochemical analyzer (Beckman Coulter, Atlanta, GA, USA), one day before surgery and on Days 1, 3, and 5 after surgery.Postoperative infectious complications:
Pneumonia: Pneumonia was defined according to the Centers of Disease Control and Prevention (CDC) guidelines [58]. Postoperative healthcare-associated pneumonia will be assessed throughout by radiograph suspicious for pneumonia, clinical signs and symptoms suspicious for pneumonia and positive culture from bronchoalveolar lavage, a positive blood culture not related to another infection, or a positive sputum culture.Postoperative infection other than pneumonia: observe the incidence of incision infection and indwelling catheter infection after the surgery (fever, bacterial culture).We will record postoperative infectious complications according to the patient’s medical history, imaging examination, clinical signs, and sputum culture within 30 days after the operation.ICU stay time: We will record the length of ICU stay after surgery (days [*d*], mean ± standard deviation [SD]).Mortality: We will record a 30-day mortality rate after surgery.The indicators of related mechanisms studied include high mobility group box 1 proteins (HMGB1), regulatory T cells (Treg), and CD4^+^ T cells. The examination methods and time points are as follows:
HMGB1: HMGB1expression level in blood samples, ELISA kit (ABCAM, Shanghai, China) one day before surgery, and on Days 1, 3, and 5 after surgeryTreg: Percentage of CD4^+^/CD25^+^ T cells in CD4^+^ T cells, flow cytometry (Becton-Dickinson, Franklin Lakes, NJ, USA), one day before surgery and on Days 1, 3, and 5 after surgeryCD4+ T cells: CD4+ T cell number/ml blood, flow cytometry (Becton-Dickinson), one day before surgery and on Days 1, 3, and 5 after surgery.

All the related indicators and the indicators of related mechanisms will be tested in the central lab of Shuguang Hospital Affiliated to Shanghai University of Traditional Chinese Medicine.

### Statistical analysis

All statistical analyses of the data will be performed using SPSS program V.21.0 (SPSS Inc., Chicago, IL, USA). A *P* value < 0.05 will be considered statistically significant. The intention-to-treat (ITT) approach will be used. Measured data will be expressed as mean ± SD (^−^*x*± *s*) if it obeys a normal distribution or an approximate normal distribution. The median (interquartile range [IQR]) will be used if the data do not obey the normal distribution and count data will be expressed in terms of the number of cases.

To analyze the primary outcome, the expression of mHLA-DR (the percentage of HLA-DR+/CD14+ cells in all CD14+ cells) will be calculated by repeated measures analysis of variance (ANOVA), and the comparisons between the two groups will be made using the Student’s *t* test. For the secondary outcomes, we will use chi-square tests for categorical data and repeated measures ANOVA or the Wilcoxon rank sum test for continuous data, according to whether the data are normally distributed. The variance analysis will be performed for the difference between the two groups and within a group. A stratified analysis will be performed to control the confounding factor if necessary. Data analysis will be conducted by statisticians who are independent of the research team.

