### Participants

#### Current sample size justification

We calculated the sample size from the pilot study in our hospital based on the primary outcome: monocytic human leukocyte antigen DR (mHLA-DR). In that study, the expression of mHLA-DR 3 days after surgery was 36.17 ± 5.42% in the TEAS group and 27.33 ± 3.50% in the Sham TEAS group, with a power of 80% and a 5% type I error rate. Assuming that the dropout rate is 10%, 88 patients (*n* = 44 for each group) are needed.

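### Intention-to-treat is promised, but the named repeated measures ANOVA in its classical form excludes any patient with a missing mHLA-DR sample; a baseline-adjusted mixed model would fit the promise better

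*Protocol article*

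**What the plan says.** Under Statistical analysis, the protocol article sets the principle: "The intention-to-treat (ITT) approach will be used". It names the software: "All statistical analyses of the data will be performed using SPSS program V.21.0". It also fixes the primary method: mHLA-DR expression "will be calculated by repeated measures analysis of variance (ANOVA), and the comparisons between the two groups will be made using the" Student's t test. Neither the SPSS procedure nor the visit or visits for the t test are given. Repeated measures ANOVA is also one of the methods for continuous secondary outcomes, depending on whether the data are normal.

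Under Primary outcome measures, blood is taken "one day before surgery, Day 1 after surgery (one day after surgery), Day 3 after surgery (3 days after surgery), and Day 5 after surgery". Under Secondary outcome measures, IL-6, IL-10, CRP, HMGB1, Treg and CD4+ counts follow the same four-visit schedule.

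The sample size section expects some loss: "Assuming that the dropout rate is 10%, 88 patients" are to be recruited, 44 per group. The planning figures come from 3 days after surgery in a pilot study.

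**The concern.** Three stated elements do not fit together: an analysis of all randomised patients, a method that in its classical form needs a complete set of visits from each patient, and an expected loss of one patient in ten. The method was chosen in the article itself, so this is a mismatch between a stated principle and a stated method, not only a detail left unsaid.

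What is at stake is the randomised comparison. If patients who lose a sample differ in mHLA-DR from those who do not, and losses differ between the arms, the analysed groups are no longer the randomised groups. The Background section makes a link between loss and outcome plausible: it associates reduced mHLA-DR after bypass surgery with longer ICU stay or ventilation and with sepsis. The ANOVA and the t tests could also rest on different sets of patients, which makes them hard to read together.

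**Working it through.** **Inputs from the article.** 88 randomised, 44 per arm; 10% dropout; four mHLA-DR visits; pilot Day 3 values "36.17 ± 5.42% in the TEAS group and 27.33 ± 3.50% in the Sham TEAS group".

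**1. The plan's own figures.** A 10% loss from 88 is 88 × 0.10 = 8.8 patients, leaving 79.2, or 39.6 per arm. The 44 per arm is consistent with about 39 or 40 evaluable patients (39/0.90 = 43.3, rounded up to 44; 40 × 1.10 = 44).

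The pilot figures themselves do not reproduce 88:
- Difference: 36.17 − 27.33 = 8.84.
- Pooled SD: √((5.42² + 3.50²)/2) = 4.56.
- Two-sided 5%, 80% power: n = 2 × (1.96 + 0.84)² × 4.56²/8.84² = 4.2, so 5 per group. Then 5/0.90 = 5.6, so 6 per group and 12 in total (14 by the noncentral t).

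That is a separate matter. Only the 88 and the 10% are needed here.

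**2. What each analysis keeps**, reading the ANOVA as using all four visits and the t tests as made visit by visit:

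| Missing sample | Classical ANOVA | t test | Mixed model on Days 1, 3, 5 |
|---|---|---|---|
| None | kept | kept at each visit | kept |
| Day 5 only | excluded | kept at Days 1 and 3 | kept |
| Day 3 only | excluded | kept at Days 1 and 5, not Day 3 | kept; contributes to the Day 3 contrast through the other visits |
| Pre-surgery only | excluded | kept, unadjusted for baseline | kept if a rule for missing baseline is set |
| All postoperative | excluded | excluded | excluded |

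**3. How many patients.** If the stated dropout is the only loss, about 9 of 88 leave the ANOVA and about 79 remain. The article gives no rate of missed single samples. As an assumption, let each of the four samples be missed independently with probability m. The number excluded is then 88 × (1 − (1 − m)⁴):
- m = 2%: 88 × (1 − 0.922) = 6.8
- m = 3%: 88 × (1 − 0.885) = 10.1
- m = 5%: 88 × (1 − 0.815) = 16.3

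If missed samples cluster in the same patients, fewer are excluded at the same m.

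**4. How much bias, by illustration only.** Assume normal values, SD 4.56, no true effect, and that the patients lost are exactly those with the lowest values. Losing a fraction f raises an arm's mean by SD × φ(z_f)/(1 − f), where φ is the normal density and z_f the normal quantile at f. The shift is 0.50 points at f = 5%, 1.25 at 15% and 1.60 at 20%. The error in TEAS minus sham is:
- 10% lost in each arm: 0
- 15% sham, 5% TEAS: 0.50 − 1.25 = −0.75, about −0.8
- 5% sham, 15% TEAS: about +0.8
- 20% sham, 0% TEAS: −1.6

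This is a deliberately extreme mechanism. The errors are small beside the pilot difference of 8.84. They are larger beside the difference that 40 per arm detects with 80% power: (1.96 + 0.84) × √(2/40) × 4.56 = 2.9 points. Against that, 0.8 is about a quarter and 1.6 somewhat over a half.

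**5. Power.** At the pilot effect, power exceeds 99.9% even with 22 per arm, so the smaller number analysed is not itself the problem.

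**The case against.** A reader might infer that the primary result will be a complete-case analysis that loses the sickest patients. The article does not support that, for four reasons.

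First, it never mentions complete cases or listwise deletion and names no SPSS procedure. Imputation before the ANOVA would be compatible with both sentences. Missing-data rules are commonly left to the full protocol or analysis plan, which are not shown, so the absence of such a rule is no fault in itself.

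Second, the sentence naming the ANOVA also names t tests between groups. Read visit by visit, these still count a patient who misses only Day 5 on Days 1 and 3, so the early data are not discarded altogether.

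Third, adding 10% for dropout does not contradict intention-to-treat. It is ordinary under that principle too, because patients without outcome data add little information under any method.

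Fourth, nothing says who misses samples or why, and no death rate by Day 5 is given. A longer ICU stay could even make sampling to Day 5 easier.

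All four hold, and they limit the point. They do not remove it. The method was named, and as named it does not by itself deliver the stated principle. The t tests only partly compensate: they leave out patients without a value at the visit tested, make no use of those patients' other visits and do not adjust for baseline.

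It can also be said that a mixed model assumes missing at random and so does not cure losses that depend on the unseen values. That is true, but the assumption is weaker than the missing-completely-at-random condition on which the t tests generally rely.

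**Conclusion.** The point holds as a mismatch between the promised principle and the named method, with a cheap and better method available. As written, and taking the ANOVA in its classical form, about 9 of 88 randomised patients could leave it at the stated 10% dropout. The figures of about 7 to 16 rest on assumed, independent per-sample missing rates of 2% to 5%. The ANOVA and the t tests could describe different patients.

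Bias requires that losses relate to outcome and differ by arm. The document establishes neither, and the size and direction cannot be derived from it; the 0.8 and 1.6 points above are illustrations under an extreme assumption. The change is worth making, but the point does not show that the trial's result will be wrong.

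**What to change.** Replace the ANOVA and the t tests for mHLA-DR by one linear mixed model (SPSS MIXED, REML) on Days 1, 3 and 5, with group, visit, group-by-visit and pre-surgery mHLA-DR. Include every randomised patient with at least one postoperative sample, in the group allocated. Read all between-group contrasts from this model, including Day 3, the visit used for the sample size. State what happens if the pre-surgery value is missing, since a covariate with a gap would otherwise remove the patient again.

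Report the number of missing samples at each visit and the number of deaths, by arm. A sensitivity analysis for deaths, for example one ranking patients who died before Day 3 worst, is optional and would probe the missing-at-random assumption. The same model can serve the laboratory secondary outcomes on this schedule where its assumptions are reasonable.

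The cost is wording in the analysis section or analysis plan, settled before allocation is disclosed, and slightly more analysis work. No further patients, samples or software are needed. The remaining weakness is the missing-at-random assumption, and patients with no postoperative sample still contribute nothing.

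### The primary analysis gives mHLA-DR both a repeated measures ANOVA and Student's t tests at an unadjusted 0.05 without saying which visit or term decides, while the sample size rests on Day 3 alone

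*Protocol article*

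**What the plan says.** Four places in the protocol article bear on this.

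- **Outcomes, Primary outcome measures.** "With mHLA-DR as the primary outcome of this clinical trial, the improvement of postoperative immunosuppression will be evaluated". The last blood sample is on Day 5; those before it are taken "one day before surgery, Day 1 after surgery (one day after surgery), Day 3 after surgery". No visit, change score or summary over visits is named as primary. The Objective section names none either.
- **Statistical analysis, method.** The expression of mHLA-DR "will be calculated by repeated measures analysis of variance (ANOVA), and the comparisons between the two groups will be made using the" Student's t test. Neither the deciding ANOVA term nor the visit for the t test is given, and no order between the two methods is stated. The section then adds between-group and within-group variance analyses, and a stratified analysis if needed, without ranking them.
- **Statistical analysis, threshold.** A P "value < 0.05 will be considered statistically significant". This is the only threshold, and no adjustment for several tests is mentioned.
- **Current sample size justification.** "In that study, the expression of mHLA-DR 3 days after surgery was" 36.17 ± 5.42% with TEAS and 27.33 ± 3.50% with sham, "with a power of 80% and a 5% type I error rate". Day 3 is not carried into the outcome or analysis sections.

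**The concern.** The outcome, analysis and sample size sections do not define the same test. The sample size describes one comparison at one visit. The analysis section describes two methods applied to an outcome with three postoperative visits, under one threshold.

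A reader of the eventual report could not tell from this text whether a significant Day 1 difference, a Day 5 difference, an overall group effect or a group-by-time interaction meets the primary endpoint. If the choice is made after the results are seen, the false-positive risk on the primary endpoint exceeds the 5% used in planning. The trial is meant to inform larger studies, so a primary result that could have been reached by several routes would be a poor basis for them.

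**Working it through.** **Inputs from the protocol article.** 44 patients per group, 10% dropout, 5% type I error, visits one day before surgery and on Days 1, 3 and 5, threshold 0.05. After dropout, 44 × 0.9 = 39.6, so about 40 per group.

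**Assumptions.** Tests are two-sided (sidedness is not stated) and data are normal. The correlation between visits is not given. It is taken as equal between all visits and varied from 0 to 0.9, with a first-order autoregressive pattern at 0.5 and 0.7 as a check.

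**Step 1: the plan's own figures.** A single Day 3 t test under no effect gives a simulated false-positive rate of 4.8% to 5.2%, so the planned 5% is right for that one test. The stated 88 patients do not follow from the pilot values. The difference is 36.17 − 27.33 = 8.84, the pooled SD is √[(5.42² + 3.50²)/2] = 4.56, and the standardized effect is 8.84/4.56 = 1.94. Then n = 2(1.960 + 0.842)²/1.94² ≈ 4.2, so 5 per group (6 with the exact t distribution) before dropout. That mismatch is a separate matter and neither supports nor weakens this point.

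**Step 2: upper reference.** For three independent t tests at 0.05, 1 − 0.95³ = 14.3%.

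**Step 3: simulation under no effect.** 40,000 trials per setting, 40 per group, four visits, each test at two-sided 0.05.

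| Correlation | Day 3 t test only | Any of 3 postoperative t tests | Any t test, ANOVA group or interaction term | t tests count only after a significant ANOVA term |
|---|---|---|---|---|
| 0 | 5.2% | 14.2% | 17.9% | 6.0% |
| 0.3 | 5.0% | 13.6% | 17.2% | 6.1% |
| 0.5 | 4.9% | 12.6% | 16.3% | 6.0% |
| 0.7 | 5.0% | 11.1% | 15.0% | 6.0% |
| 0.9 | 4.8% | 8.3% | 12.7% | 5.3% |

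Under the autoregressive pattern, the third and fourth columns give 11.5% to 12.8% and 16.3% to 16.7%. The last column rises to at most 6.4%.

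**Step 4: what restores 5%.** Day 3 alone gives 4.8% to 5.2%. The ANOVA group effect alone gives 4.9% to 5.2%. Three postoperative t tests at 0.05/3 = 0.0167 give 3.0% to 5.1%.

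**Step 5: power.** With the pilot effect and 40 per group, power exceeds 99.9% even at 0.0167. With a quarter of it (8.84/4 = 2.21 percentage points), power is 58% at 0.05 and 41% at 0.0167. If the true effect is much smaller than in the pilot, one named test at 0.05 therefore keeps more power than splitting the error over three visits.

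**The case against.** **The text does not say that any one test wins.** A reader might infer that a t test will be run at every visit and that one significant result is enough. The article does not state the number of t tests, their visits, or a rule that any one suffices. This objection stands, so the rates of 8% to 18% are conditional on that use of the tests. It does not remove the point, because the article also gives no rule that would exclude that use.

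**A benign reading exists.** An ANOVA followed by t tests can be taken as an overall test with follow-up comparisons, which gives about 5% to 6%. This is a fair reading, but the dependence is not written.

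**The planned 5% does hold for a Day 3 test.** It would be wrong to say that the 5% in the sample size paragraph is false. The Day 3 basis also hints at the intended visit. A hint in the sample size paragraph is not a designation, however, and the outcome and analysis sections do not take it up.

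**Day 1 as a weak visit.** A reader might add that Day 1 tests the full course poorly because the fourth postoperative session falls at 23–24 h. No clock time is given for the Day 1 sample, and the matter has no bearing on how many tests are made. It is not part of this point.

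**The trial is preliminary, and an analysis plan may exist.** A separate plan could rank the visits. But the article is not silent here: it states the primary analysis, and does so with two unranked methods.

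**Conclusion.** The point holds in this form: the article assigns one primary outcome two methods at an unadjusted 0.05 and names no deciding visit, ANOVA term or order of testing, while the trial is sized on Day 3 alone.

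The size depends on how the tests are used:

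- about 5% if Day 3 alone decides;
- about 5% to 6% if the t tests count only after a significant ANOVA term;
- about 8% to 14% if any of three postoperative t tests may count;
- about 13% to 18% if either ANOVA term may count as well.

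These figures rest on 40 per group, normal data, two-sided tests and an assumed correlation between visits of 0 to 0.9. The documents do not establish that the sponsor intends the looser use; they leave it open.

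**What to change.** Before unblinding, state one primary contrast in both Primary outcome measures and Statistical analysis. The preferred choice is the between-group comparison of mHLA-DR at Day 3, two-sided at 5%, because the sample size already uses that visit. One named ANOVA effect would serve equally for error control, provided that the visits entering it are stated and the sample size basis is rewritten to match. Label the remaining visits and ANOVA terms as secondary.

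The cost is a few sentences in a dated amendment. The article is the third protocol version, with recruitment due to end on December 31, 2019. Assignments stay undisclosed until the end of the study, so the amendment should record that it was made blind. The downside is that an effect seen only at another visit can no longer be claimed as a primary success.

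### The preoperative mHLA-DR value is given no role as a covariate; adjusting the Day 3 comparison for it would give a sharper and better-defined primary estimate at no cost

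*Protocol article*

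**What the plan says.** All of this comes from the protocol article.

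- **Primary outcome measures.** "Peripheral blood is collected from the patient to test this indicator at the following time points: one day before surgery, Day 1 after surgery"; the list goes on to Days 3 and 5. The preoperative value is thus one of four time points for the primary outcome. Under Interventions, the first stimulation is given shortly before anesthesia, so the sample from the day before surgery precedes any treatment.
- **Statistical analysis, model.** mHLA-DR "will be calculated by repeated measures analysis of variance (ANOVA"). No covariate is named, nor the visits that enter, nor the term that answers the primary question.
- **Statistical analysis, group comparison.** "the comparisons between the two groups will be made using the Student’s *t* test". Whether raw values or changes are compared is not stated.
- **Statistical analysis, adjustment.** "A stratified analysis will be performed to control the confounding factor if necessary". The confounder, the strata and the criterion are not given.
- **Current sample size justification.** The size rests on Day 3: "the expression of mHLA-DR 3 days after surgery was 36.17 ± 5.42% in the TEAS group" against "27.33 ± 3.50% in the Sham TEAS group".

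**The concern.** A value taken before treatment cannot carry a treatment effect. In a randomized trial its expected group difference is zero, and its useful role is to explain between-patient variation in the later values. The plan collects this value but assigns it no such role.

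This has two consequences on the natural reading of the text, which is a four-visit ANOVA plus t tests on raw values. First, the group main effect mixes three postoperative visits with one at which the true difference is zero, so it does not estimate the postoperative effect. Second, the t tests leave in the error term the variation that baseline would explain. Meanwhile the only route to adjustment is a conditional one with no stated trigger.

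The article presents the trial as preliminary work meant to inform larger trials. Its main product is therefore the size of the mHLA-DR effect and its interval, which makes a clear target and good precision matter more than the P value.

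**Working it through.** **Inputs from the article.** Four visits, one of them preoperative. Day 3 pilot means 36.17 (SD 5.42) and 27.33 (SD 3.50). 44 per arm with 10% dropout: 44 × 0.9 = 39.6, taken as 40 evaluable per arm.

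**Assumptions, not in the documents.** Equal variances; one common correlation r between all visits, tried at 0.3, 0.5 and 0.7; the same effect on Days 1, 3 and 5 wherever visits are averaged; two-sided 5% test.

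**The plan's own figure.** The article gives no figure for baseline adjustment. Its total of 88 does not follow from the pilot values (these give about 5 per arm before dropout). That is a separate matter and is not used here.

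**Step 1. Pilot effect.** Difference = 36.17 − 27.33 = 8.84. Pooled SD = √[(5.42² + 3.50²)/2] = 4.56. Standardized effect = 8.84/4.56 = 1.94.

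**Step 2. Dilution of the group main effect.** If all four visits enter, the group term estimates (0 + δ + δ + δ)/4 = 0.75δ. On the pilot figures, 0.75 × 8.84 = 6.63 points.

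**Step 3. Day 3 precision.** Adjusting for baseline multiplies the residual variance by 1 − r², and the interval width by √(1 − r²). The unadjusted 95% half-width is about 1.96 × 4.56 × √(2/40) = 2.00 points.

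| r | 1 − r² | Interval narrower by | Adjusted half-width (points) |
|---|---|---|---|
| 0.3 | 0.91 | 4.6% | 1.91 |
| 0.5 | 0.75 | 13.4% | 1.73 |
| 0.7 | 0.51 | 28.6% | 1.43 |

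**Step 4. Power at the pilot effect.** Power = Φ(effect/√(2 × variance/40) − 1.96). For the plain Day 3 t test the ratio is 8.84/(4.56 × √(2/40)) = 8.7. The four-visit main effect has variance factor (1 + 3r)/4. At r = 0.7 this is 0.775, and the ratio is 6.63/(4.56 × √0.775 × √(2/40)) = 7.4. Both exceed 99.9% power, as do the adjusted analyses.

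**Step 5. Power at a smaller effect, for comparison only.** Take 0.626 SD, chosen so that the Day 3 t test has 80% power with 40 per arm.

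| Analysis | Effect | Variance factor | r = 0.3 | r = 0.5 | r = 0.7 |
|---|---|---|---|---|---|
| Four-visit group main effect | 0.75δ | (1 + 3r)/4 | 86.2% | 75.7% | 66.5% |
| Day 3, baseline-adjusted | δ | 1 − r² | 83.6% | 89.9% | 97.5% |
| Postoperative mean minus baseline | δ | (1 + 2r)/3 − 2r + 1 | 82.6% | 92.9% | 99.3% |
| Postoperative mean, unadjusted | δ | (1 + 2r)/3 | 97.0% | 92.9% | 87.9% |
| Postoperative mean, baseline-adjusted | δ | (1 + 2r)/3 − r² | 98.8% | 99.1% | 99.9% |

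The last two rows show that much of the advantage of the adjusted postoperative mean comes from averaging three visits. At r = 0.3, adjustment itself adds about 2 percentage points (97.0% to 98.8%); at r = 0.7 it adds 12 (87.9% to 99.9%).

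**The case against.** The strongest reply is that the article does not say which visits enter the ANOVA, which term is tested, or whether the t tests use changes. Covariates and contrasts are often left to an analysis plan, and one may exist. That stands, and it makes the dilution conditional. What the article does fix is the pair of methods, and neither as written gives the baseline a covariate role.

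Three further replies have force. An unadjusted t test is unbiased under randomization. A group-by-time term uses the preoperative visit and is not diluted in this way. And at r = 0.3 the four-visit main effect (86.2%) has slightly more power than the adjusted Day 3 comparison (83.6%), because it averages visits; at 0.5 and 0.7 the order reverses.

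A reader might infer that the trial's result will be biased by a quarter. The documents do not support that: it needs all four visits in the model, the group main effect as the test, and a constant effect over Days 1, 3 and 5, none of which is stated. A reader might also infer that adjustment will be chosen after looking at the results. The article gives no timing or criterion for that decision, and it says that the analysts are blinded to allocation and independent of the research team, which limits the risk. The loose wording remains, but not proof of a data-driven choice.

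**Conclusion.** The point holds as a free improvement in precision and clarity, not as an error that invalidates the analysis. No baseline covariate is planned for the primary outcome, although the value is collected. Adjustment would narrow the Day 3 interval by about 5%, 13% or 29% at correlations of 0.3, 0.5 or 0.7; the documents give no correlation, so this range is an assumption. If the four-visit group main effect were taken as the result, a constant postoperative effect would be reported at three quarters of its size.

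It would be tempting to conclude that the trial is underpowered without adjustment. At the article's own pilot effect, power is above 99.9% under every analysis considered. Power would differ materially only if the true effect were far smaller, near 0.63 SD instead of 1.94 SD.

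**What to change.** In the Statistical analysis section, state that the primary estimate is the group difference in mHLA-DR on Day 3, the visit used for the sample size, with its 95% confidence interval, from a model with preoperative mHLA-DR as covariate. Either of these will do:

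- ANCOVA on the Day 3 value; or
- a mixed model on Days 1, 3 and 5 with arm, visit, arm-by-visit and baseline, reading off the Day 3 contrast.

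State that the preoperative value is not entered as an outcome in a group main effect. For the primary outcome, let this prespecified adjustment replace the sentence on conditional stratification.

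The cost is wording in the protocol or analysis plan, settled before allocation is disclosed to the analysts. The preoperative sample is already scheduled, so no extra visit, assay or patient is needed.
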